The efficacy of albendazole is variable against *Trichuris trichiura* compared to other anthelmintics; the cure rate ranges between 2.6 and 64.5% [8] and the egg reduction rate ranges between 7 and 83.1%. However, high cure rates of *Trichuris trichiura* are observed in some contexts [9–11]. In a study conducted in the Peruvian Amazon, an open-pair randomized trial was conducted in fifth-grade children from 18 primary schools (9 intervention and 9 control). Intensity of *Ascaris lumbricoides* infection at follow-up was 58% lower in children from intervention schools, a significant reduction as compared to children from control schools (RR = 0.42; 95% CI 0.21 to 0.85), but no significant changes were observed in the intensity of hookworm or *Trichuris trichiura* [12]. In another study from Peru, a total of 1193 school-age children were dewormed with a single dose of Albendazole (400 mg). Of the 909 children who tested positive for at least one STH infection, a random sample of 385 were followed up 2 weeks later with a second stool sample. The efficacy of albendazole was variable, with an egg reduction rate of 99.8% for *Ascaris lumbricoides* (95% CI 99.3–100); 93.6% for hookworm (95% CI 88.2–96.6), and 72.7% for *Trichuris trichiura* (95% CI 58.5–79, 1) [13]. In many cases treatment with albendazole alone appeared inadequate, especially for *Trichuris trichiura*. Other interventions such as combined therapy have been evaluated in other contexts. Ivermectin results in higher cure rates than albendazole and is well tolerated. The benefits of ivermectin for helminth infections would depend on the amount of resistance present [14–16].

Large-scale interventions to control soil-transmitted helminth infections at the community level with anthelmintic drugs such as albendazole have the potential to exert selective pressures which may favor the development of drug resistance, which could significantly reduce the benefits provided by deworming programs. Drug resistance in parasitic nematodes is caused by a single nucleotide polymorphism (SNP) in the β-tubulin gene at codon positions 200 (T → A), 167 (T → A) or 198 (A → C) [17].

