Direct observation: In a properly labeled slide, 0.5 g of feces will be applied with a wooden applicator and 20 µL of saline solution will be added. The first observation will be made from left to right, then the procedure will be repeated with 20 µL of Lugol’s solution added. Both observations will be made with the 10× and 40× objectives in order to qualitatively identify the absence or presence of helminths (*Ascaris lumbricoides*, *Trichuris trichiura*, hookworms, and *Strongyloides stercoralis*).Kato-Katz method: Two grams of feces will be placed on a smooth and sterile surface, covered with a piece of nylon and pressed with a flat-edge plastic applicator. The filtered feces will then be placed in the center of a 41.7 mg template on a slide until the hole is filled, after which the template will be removed and the sample will be covered with a cellophane sheet previously imbued in a glycerol-blue solution of methylene, and pressure will be applied until the sample is distributed homogeneously. After a 30-min incubation, eggs counts will be carried out using the 10× objective and a cell counter, the total number of eggs counts per species will be reported in eggs per gram (epg) and will be multiplied by 24 (41.7 mg template) [27], and the results of each parasite found will be recorded and reported quantitatively. This procedure will be performed on the 4 samples per subject collected throughout the study [28].STH infection by qPCR: To measure the intensity of the infection, quantitative polymerase chain reaction (qPCR) will be used in such a way that the Kato-Katz variability between users is reduced and the sensitivity of the detection of low-grade parasitic infections is increased [29, 30]. Real-time multiplex qPCR will be performed on positive samples (Day 0) for helminths that were identified by direct observation and Kato-Katz for the simultaneous detection of *Ascaris lumbricoides*, *Trichuris trichiura*, *Necator americanus*, *Ancylostoma duodenale*, and *Strongyloides stercoralis* [31]. If the sample from Day 0 is negative, the sample from Day 15 will be analyzed if it is positive for helminths. Amplification will be performed in a Quant Studio 7 Flex thermocycler (Applied biosystems) in a total volume of 25 µL using GoTaq® qPCR Probe Master Mix (Promega, USA) and 5 µL of fecal DNA. There will be two multiplex qPCR assays (STH1 and STH2); STH1 will be used to detect *Ascaris lumbricoides*, *Trichuris trichiura* and *Strongyloides stercoralis*, while STH2 will be used for the 3 species of hookworms. The cycling conditions for both cases will be the following: 1 cycle at 95 °C for 5 min, 40 cycles at 95 °C for 10 s and 1 cycle at 60 °C for 60 s. The primers will be the same ones used by Azzopardi et al. [32] which can be seen in Table 1.**Table 1 Tab1:** Primers used in multiplex qPCR analysis of stool samples by STH1 and STH2

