### Statistical analysis

Data will be analyzed in Access using Stata, using chi square, Fisher’s exact, and Wilcoxon tests to compare frequencies between groups. To analyze the data from direct observation and quantification by the Kato-Katz method, descriptive statistics will be used, to report the prevalence found in percentages. For the sociodemographic and clinical data of the study population, measures of central tendency and dispersion will be used for the quantitative variables and measures of relative frequency for the qualitative variables. Comparisons will also be made between sample 1, sample 2, sample 3 and sample 4 to determine the positivity of each species of parasite found using the Yates chi-square test, setting a significance level of p < 0.05.

The sociodemographic variables will be compared with the parasite load and presence/absence of parasites, using a multiple logistic regression model (univariate t-test), to determine the variables statistically associated with infection by *Ascaris lumbricoides*, *Trichuris trichiura* and hookworms.

The quantification performed with the Kato-Katz method will be compared with the Ct value (Ct threshold) of the multiplex qPCR, by converting Log10 of the absolute egg count per stool sample, in order to estimate the absolute egg counts in eggs per gram (EPG) in the DNA extractions, using the following formula [33]:$${\text{EPG}}\;{\text{Ascaris}} = 10\left( {{\text{Ct}} - 36.97} \right)/ - 3.489,$$$${\text{EPG}}\;{\text{Trichuris}} = 10\left( {{\text{Ct}} - 36.73} \right)/ - 3.288,$$$${\text{EPG}}\;N.\;americanus = 10\left( {{\text{Ct}} - 35.02} \right)/ - 3.641,$$$${\text{EPG}}\;A.\;duodenale = 10\left( {{\text{Ct}} - 35.02} \right)/ - 3.641.$$

To determine treatment efficacy, the prevalence will be measured before and after receiving treatment and compared using the Yates chi-square test. For calculations of cure rate and intensity of infection obtained from qPCR, only data from positive results before taking the first dose will be included [34].

The cure rate will be measured using the following formula:$$\frac{{\# \;{\text{positive}}\;{\text{for}}\;{\text{helminths}}\;\left( {{\text{pretreatment}}} \right) - \# \;{\text{negative}}\;{\text{for}}\;{\text{helminths}}\;\left( {{\text{post}}\;{\text{treatment}}} \right)}}{{\# \;{\text{cases}}\;{\text{positive}}\;{\text{for}}\;{\text{helminths}}\;\left( {{\text{pretreatment}}} \right)}} \times 100.$$

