Intensity of infection will be measured using the following formula:$$\frac{{{\text{mean}}\;{\text{egg}}\;{\text{count}}\;\left( {{\text{pretreatment}}} \right) - {\text{mean}}\;{\text{egg}}\;{\text{count}}\;\left( {{\text{post}}\;{\text{treatment}}} \right)}}{{{\text{mean}}\;{\text{egg}}\;{\text{count}}\;\left( {{\text{pretreatment}}} \right)}} \times 100.$$

And the calculation of the rate of reduction of eggs by helminth species:$$\frac{{\left[ {1 - {\text{mean}}\;{\text{egg}}\;{\text{count}}\;{\text{in}}\;{\text{EPG}}\;\left( {{\text{post}}\;{\text{treatment}}} \right)} \right]}}{{{\text{mean}}\;{\text{egg}}\;{\text{count}}\;{\text{in}}\;{\text{EPG}}\;\left( {{\text{pretreatment}}} \right)}} \times 100.$$

In addition, a comparison of the cycle threshold (Ct) by qPCR will be made using the Student’s t-test for paired samples.

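### The egg-reduction-rate formula has a misplaced bracket, so it does not yield a reduction rate and contradicts the formula printed directly above it

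*Protocol article*

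**What the plan says.** The Statistical analysis section of the protocol article ends with two formulas built from mean egg counts before and after treatment.

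- The first is introduced by "Intensity of infection will be measured using the following formula" and is printed as (pre − post)/pre × 100.
- The second is introduced by "And the calculation of the rate of reduction of eggs by helminth species". Its numerator is a closed bracket holding 1 minus the mean post-treatment EPG, its denominator is the mean pretreatment EPG, and the result is multiplied by 100.

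Three other statements bear on the size of the problem. In Laboratory analysis, each Kato-Katz count "will be multiplied by 24 (41.7 mg template"), so one egg on the slide is 24 EPG. For cure rate and qPCR intensity, "only data from positive results before taking the first dose will be included". The Background cites an earlier Peruvian study with "an egg reduction rate of 99.8% for *Ascaris lumbricoides* (95% CI 99.3–100); 93.6% for hookworm (95% CI 88.2–96.6), and 72.7% for *Trichuris trichiura".

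**The concern.** The printed numerator subtracts an egg count from a bare 1. It should be the ratio of the two means that is subtracted from 1. As printed, the quantity is not a reduction rate: it has no fixed value for complete clearance, and it changes with the unit of counting.

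The two formulas take the same kind of input and give different answers, and the article does not say which governs. An analyst who coded the second one literally would report figures near zero or below it for a drug that had removed most eggs. Those figures could not be set beside the egg reduction rates in the Background. Albendazole resistance is one of the two major outcomes, so a per-species egg reduction figure is one that readers will look for.

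**Working it through.** **Inputs.** The article states no egg reduction figure of its own and no mean pretreatment EPG, so there is no plan figure to reproduce. The true rates used are the three cited in the Background (99.8%, 93.6%, 72.7%), plus 100% (full clearance) and 0% (no effect). The pretreatment mean is an assumption, shown from 24 to 5,000 EPG. The lower end is one egg on the slide, the least that a mean over children positive on Kato-Katz can be.

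**Formulas.** Write pre and post for the two means and R for the true rate, R = (1 − post/pre) × 100.

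- Upper formula: (pre − post)/pre × 100 = (1 − post/pre) × 100 = R.
- Lower formula as printed: (1 − post)/pre × 100 = 100/pre − 100 × post/pre = 100/pre − (100 − R).

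The two agree only if 100/pre = 100, that is, pre = 1 EPG. The printed value cannot exceed 100/pre, and it is negative whenever post is above 1 EPG.

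**Worked case, pre = 500 EPG (assumed).**

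- R = 99.8%: post = 1.0; (1 − 1.0)/500 × 100 = 0.0%.
- R = 93.6%: post = 32.0; (1 − 32.0)/500 × 100 = −6.2%.
- R = 72.7%: post = 136.5; (1 − 136.5)/500 × 100 = −27.1%.

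**Range of the printed value.**

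| Assumed pre (EPG) | R = 100% | R = 99.8% | R = 93.6% | R = 72.7% | R = 0% |
|---|---|---|---|---|---|
| 24 | 4.2% | 4.0% | −2.2% | −23.1% | −95.8% |
| 100 | 1.0% | 0.8% | −5.4% | −26.3% | −99.0% |
| 500 | 0.2% | 0.0% | −6.2% | −27.1% | −99.8% |
| 5,000 | 0.02% | −0.18% | −6.38% | −27.28% | −99.98% |

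The upper formula returns R in every cell.

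**Unit check.** A reduction rate should not depend on whether eggs are counted per slide or per gram. A mean of 500 EPG is 500/24 = 20.83 eggs per slide. At full clearance the printed formula gives 100/500 = 0.2% in EPG but 100/20.83 = 4.8% in slide counts. The upper formula gives 100% in both.

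**The case against.** The strongest reply is that this is a transcription slip with little practical risk. The correct expression stands directly above, a bare 1 minus an EPG mean is visibly odd, and a literal run giving about 0% for *Ascaris* beside a cited 99.8% would be noticed. No code is shown, and an unseen analysis plan may have the right form. Much of this stands: the slip is easy to spot and easy to repair. But the printed text is still a stated analysis rule that gives a wrong answer if followed, and nothing in the article tells the reader that the upper formula replaces the lower one. The bracket and the fraction are explicit in the equation, so the error is not a loss in reading the PDF.

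One could also argue that the upper formula is meant for qPCR-derived counts and the lower for Kato-Katz counts, so that the two never meet on the same data. The article does not say so, and the lower formula would be wrong for either source.

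A reader might infer more than the article supports, in three ways.

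- *That this is the main efficacy measure.* The article ties treatment efficacy to prevalence before and after treatment, compared by the Yates chi-square test. The sample size section defines resistance by detection of any helminth at follow-up. Neither rests on egg reduction.
- *That full clearance could print a negative value.* It cannot: with post = 0 the result is 100/pre, which is small but positive.
- *That clearance cannot be told from failure.* For a given pretreatment mean the printed value is the true rate shifted by a constant, so clearance and no effect stay 100 points apart (0.2% against −99.8% at 500 EPG). It is the level that is wrong.

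**Conclusion.** The point holds: the per-species egg reduction formula is wrong as printed and conflicts with the one above it. The error is 100 − 100/pre percentage points at every true rate, which is 95.8 points at a mean of 24 EPG and 99.8 points at 500 EPG.

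The exact printed values depend on the assumed pretreatment mean; the conclusion does not. The 24 EPG floor assumes that the mean is taken over children with a positive Kato-Katz count. Averaging over all children, or using qPCR-derived EPG, could give a lower mean. At 3 EPG, for instance, full clearance would print 100/3 = 33%, still not 100%.

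The reach is limited. This is the only formula labelled by species, but the article attaches no test to it and the sample of 380 does not depend on it. It should be corrected because it is a stated outcome formula that cannot be used as written.

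**What to change.** 1. Replace the formula with egg reduction rate = [1 − (mean post-treatment EPG / mean pretreatment EPG)] × 100, for each helminth species.
2. Reconcile the label of the formula above it. Once the bracket is corrected the two are the same quantity, and a percentage reduction is not an intensity of infection. Either keep one formula under the egg reduction label, or, if two sources of counts are meant, say which formula applies to which.
3. Check that the analysis code uses the corrected form. With post = 0 it must return 100% whatever the pretreatment mean, and with post = pre it must return 0%.

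The cost is one corrected equation, one label and a short code check. No design element, sample size or data collection changes.

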## Discussion

Data from observational clinical efficacy studies such as this one are vitally important to assure continued high levels of geohelminth infection control, and to permit re-evaluation of clinical guidelines when necessary to achieve desired program goals.

## Data Availability

Data generated from this study will be available from the corresponding author on reasonable request, or published with the final results, after all findings are available. Data will be shared after approval of a proposal by the authors for legitimate scientific purposes.

## Abbreviations

STH: Soil-transmitted helminths
WHO: World Health Organization
PAHO: Pan American Health Organization
PC: Preventive chemotherapy
qPCR: Quantitative polymerase chain reaction
STH1 and STH2: Two multiplex qPCR assays for detection of geohelminths
DNA: Deoxyribonucleic acid
